### Additional analyses

Given the potential for effect modification and compositional changes in the study populations, subgroup analyses by parents’ sociodemographic characteristics (ie, annual labour income, to determine eligibility for earnings based benefits or educational attainment) will be considered for all RQ. Analyses by parents’ nativity will be implemented for RQ#2–4, given differential responses to the policies by Swedish-born and foreign-born parents.^14^ Other relevant parental characteristics, that is, age at childbirth and cohabitation status, will also be considered.

Sensitivity analyses will be performed to account for systematically missing data, such as maternal weight (ie, given that women appearing to be of normal weight are less monitored for obesity).^47^ For studies examining first births, sensitivity analyses restricting mental health outcomes to the 18 months post birth will be considered in order to exclude the potential health effects related to a second pregnancy.

For all ITS designs, we will specify multiple intervention points to assess the possibility of lagged policy effects. Robustness analyses of falsification (‘pseudo-intervention’) dates and falsification outcomes (eg, prebirth hospitalisations) will also be considered.

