#### Policy reforms

The Swedish parental leave system has undergone several reforms over the past half-century. We define a ‘policy reform’ as any change implemented at a specific time that could impact either uptake or sharing of parental leave, as well as eligibility for earnings based benefits. To evaluate the unforeseen health consequences of the parental leave policy—that is, a welfare policy that does not primarily target health—we will concentrate on reforms that have either been shown to accomplish their primary aim (ie, the speed premium, father’s quota and double days reforms) or with undoubtedly significant, although unintended, impacts (ie, the doubled value of general flat-rate benefits).

Doubled flat-rate benefits: Although not explicitly a reform, the doubling of the general flat-rate benefits from 60 SEK per day (from 1987) to 120 SEK per day (in 2002) aimed to secure the economic welfare of low-income families.

Speed premium: Since earnings related parental leave benefits are estimated based on one’s salary prior to childbearing (at approximately 80% of the salary), parents having children in quick succession may choose to temporarily reduce their working hours or be unable to return to work at all and will thus have lower benefits for their second and subsequent births. In 1980, a supplement (commonly referred to as the ‘speed premium’) was introduced to safeguard women’s income between parental leave periods, ensuring that for births with up to 24 months’ spacing^13^ and then with up to 30 months’ spacing (following a 1986 expansion),^14^ all earnings based benefits could be based on the parents’ salaries prior to the birth of their previous child, if higher than their current income. An evaluation of the 1986 expansion revealed that an increased proportion of Swedish-born parents had children in short succession; even if this was an unintended consequence, the reform has henceforth been called the ‘speed premium’.^14^

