### Unintended health consequences of the Swedish parental leave system

Despite the relative generosity of the Swedish parental leave system and its efforts to promote gender equity, some aspects could be responsible for the maintenance or increase in social and health inequities. For example, the strong work-eligibility requirement for earnings based parental leave benefits may exclude groups with less stability in the labour market, such as students and migrants, from benefits equal to those enjoyed by persons with stable incomes.^17^

Inequities in the work-eligibility requirement can emerge in various ways, either by restricting the parental leave benefits scheme to the securely employed and coincidentally excluding parents with ill health (ie, health selection) or by creating health inequities through the unequal distribution of benefits (ie, social causation). For example, individuals with long-term illness may be more likely to have a weak labour market attachment, which in turn can exclude them from earnings related parental leave benefits, thus further increasing socioeconomic inequities. Based on this, we expect that the doubled flat-rate benefits could increase leave uptake among lower-income families or decrease the economic trade-off of using parental leave among lower-income families, thus having potential psychosocial benefits.

Parental leave policies might impact health differently following certain policy reforms. For example, the speed premium supplement introduced to secure earnings based parental leave benefits to parents who have children in quick succession essentially incentivises short birth spacing.^14^ This might lead to increased psychosocial stress and adverse reproductive outcomes among women who become pregnant while simultaneously rearing an infant or toddler. The WHO recommends a minimum of 24 months, assuming 9 months of gestation, before a new conception to avoid adverse reproductive outcomes.^18^ Short birth intervals have been associated with nutrition depletion,^19^ as the mother might not have enough time between births to recover her nutritional reserves and higher risks of weight gain and obesity throughout life.^20^ In turn, these issues are risk factors for adverse outcomes in subsequent children, including low birth weight, preterm birth and perinatal death.^18 21^

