### Outcomes

Child health outcomes include low birth weight (<2500 g, irrespective of gestational age), preterm birth (<37 gestational weeks) and a small-for-gestational age measure (<10th percentile of birth weight for each gestational age, based on sex-specific Swedish reference curve for normal foetal growth)^41^ from the MBR; hospitalisation episodes of respiratory tract infections during the first 2 years of life (International Classification of Diseases-10 (ICD-10) Codes J20.5, J21.0, J21.9, J20.9, J18.9, J12.9 and J22.9) from the NPR and duration of partial or exclusive breast feeding (at months 2, 4, 6, 9 and 12) as well as childhood obesity (body mass index (BMI); weight in kilograms/height in meters^2^ using age-specific and sex-specific cut-offs for children’s overweight and obesity^42 43^ at 18 months and 3–5 years) from the CHR. Maternal health outcomes include maternal early pregnancy overweight (BMI 25–29.9 kg/m^2^) and obesity (BMI 30–39.9 kg/m^2^).^44^

Mental health outcomes will be assessed for both parents using count data on purchases of prescription anxiolytic and antidepressant medications (Anatomical Therapeutic Classification Codes N05B and N06A, respectively) as well as outpatient visits and hospitalisations with a primary diagnosis of mental and behavioural disorders (until 1997, ICD-9 Codes 290–319; thereafter, ICD-10 Codes F00-F99), from childbirth to 18 and 36 months after birth.

Outcomes will be expressed as prevalence or rates, given availability of follow-up time.

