RQ#3: We will conduct an ITS analysis of parents of children born before and after the 1995 father’s quota reform using segmented regression to capture changes in psychiatric hospitalisation rates up to 36 months after childbirth, based on fathers’ eligibility for the father’s quota.

RQ#4: An ITS for parents to children born before and after the 2012 double days reform will be implemented to capture changes in the number of outpatient visits for mental health and psychotropic prescriptions within 36 months after childbirth, by child’s month of birth.

RQ#5: We will implement separate ITS analyses of children born before and after the 1995 father’s quota and 2012 double days reforms, comparing hospitalisation rates for diagnoses of respiratory tract infections (in children under 2), prevalence of childhood obesity (at 18 months and 3–5 years) and changes in breastfeeding duration.

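### The 18-month restriction shortens the overlap with a second pregnancy but does not exclude it: any birth interval under 27 months still places pregnancy time inside the window

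*Protocol article*

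**What the plan says.** The Outcomes section of the protocol article measures both parents' mental health "from childbirth to 18 and 36 months after birth". Under Study design and statistical analyses, RQ#3 looks for "changes in psychiatric hospitalisation rates up to 36 months after childbirth", and RQ#4 counts "outpatient visits for mental health and psychotropic prescriptions within 36 months after childbirth".

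The Additional analyses section then offers a sensitivity analysis for first-birth studies. It limits mental health outcomes to "18 months post birth will be considered in order to exclude the potential health effects related to a second pregnancy". The article mentions no censoring at the next conception and no removal of parents who conceive again, so the shorter window is the only device given for that purpose.

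Two other places bear on the point. The section on unintended health consequences reasons about spacing "assuming 9 months of gestation". The Policy reforms section describes the speed premium as protecting benefits "for births with up to 24 months’ spacing" from 1980, extended to 30 months in 1986. It reports that short spacing became more common among Swedish-born parents after the 1986 expansion.

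**The concern.** A fixed window after the first birth excludes a second pregnancy only if no second conception falls inside it. At 18 months that fails for the shorter birth intervals, including every interval within the 24-month limit of the 1980 speed premium and most of the range up to the 30-month limit of 1986.

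What is at stake is the inference drawn from the check. Psychotropic purchases and psychiatric contacts can change during pregnancy. If a leave reform also changes when couples have their next child, part of a measured effect on mental health could run through the second pregnancy. The 18-month analysis is the article's stated protection against that reading. If it is taken at its word, similar results at 18 and 36 months would be reported as showing that second pregnancies play no part, and a window that still contains pregnancy time cannot show that alone.

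**Working it through.** **Inputs**
- Sensitivity window W = 18 months (Additional analyses); main follow-up W = 36 months (RQ#3 and RQ#4).
- Gestation g = 9 months (section on unintended health consequences).
- Speed premium limits: 24 months (1980) and 30 months (1986) (Policy reforms).
- Distribution of birth intervals: not given.

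The article derives no figure on this point, so there is none to reproduce.

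**Formulas**, for a birth interval I:
- Month of second conception = I − g.
- A second pregnancy overlaps the window when I − g < W, that is, I < W + g.
- Pregnancy months inside the window = max(0, min(W, I) − (I − g)).

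**Thresholds**
- 18-month window: 18 + 9 = 27 months.
- 36-month window: 36 + 9 = 45 months.

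**By interval, 18-month window**

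| Interval (months) | Second conception (month) | Pregnancy months inside |
|---|---|---|
| 18 | 9 | 9 |
| 20 | 11 | 7 |
| 22 | 13 | 5 |
| 24 (1980 limit) | 15 | 3 |
| 26 | 17 | 1 |
| 27 | 18 | 0 |
| 30 (1986 limit) | 21 | 0 |

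**Sensitivity to the gestation figure.** With 38 weeks from conception (8.74 months) the threshold is 26.7 months. For a birth at 37 gestational weeks, taken as 35 weeks from conception (8.05 months), it is 26.1 months. The conclusion does not change.

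**What the restriction achieves.** It removes all overlap for intervals from 27 up to 45 months. It also removes the time after the second birth for every interval of 18 months or more. It leaves pregnancy time in the window for intervals under 27 months.

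**Illustration only; every input is an assumption.** Take log-normal intervals with median 30 to 42 months and log-SD 0.4 to 0.5, and let 80% of first-time parents have a second child.
- Share of second births conceived before month 18: 13% to 42%.
- Share of follow-up time at or after second conception: 3% to 14% of the 18-month window, against 15% to 32% of the 36-month window.
- Reduction in affected months from shortening the window: 78% to 91%.

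**The case against.** The strongest reply is that the check is informative although imperfect. Many overlaps are short (1 month at a 26-month interval), and in the illustration the shorter window removes most of the affected time. Comparing two windows that differ so much in contamination tells the reader something. This stands. It supports the word *reduce*; it does not make *exclude* true.

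Second, in an interrupted time series a stable level of second pregnancies on both sides of the reform is absorbed by the level and trend terms. Bias needs spacing to change at the reform, and the article reports no such change at the 1995, 2002 or 2012 reforms. Its evidence on spacing belongs to the speed premium, which is studied under RQ#2 with other outcomes. This also stands. It limits the consequence and leaves the question unanswered for the three mental health reforms.

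Third, this is an optional sensitivity analysis in a condensed article, and censoring detail may sit elsewhere. That is fair for technical detail. The purpose claimed for the window is stated in the article, however, and the window as described does not meet it.

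A reader might infer three stronger things that the document does not support:
- That a known, large share of parents is affected. No spacing distribution is given, and the illustration's threefold range comes from chosen inputs.
- That both 24- and 30-month spacings are described as increasingly common. The rise is reported for the 1986 expansion only, and a 30-month interval is conceived at month 21, outside the window.
- That the check is worthless or the 36-month results are invalid. Neither follows.

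**Conclusion.** The point holds in limited form. On the article's 9 months of gestation, the 18-month restriction lowers the interval below which a second pregnancy overlaps follow-up from 45 to 27 months. It reduces second-pregnancy time and does not exclude it, so agreement between the two windows is not enough to dismiss second pregnancies as an explanation.

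The threshold rests only on calendar arithmetic and moves by less than one month under the shorter gestations tried. The number of parents affected, and any resulting bias, cannot be computed from the article. Material bias depends mainly on spacing shifting at a reform date, which is unknown here and can be checked in the data. The correction goes beyond wording, because it changes what the sensitivity analysis can conclude.

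**What to change.** 1. In Additional analyses, describe the 18-month restriction as reducing, not excluding, effects related to a second pregnancy.
2. For each mental health reform analysis, report the share of first-time parents with an estimated next conception before 18 and before 36 months, separately on each side of the reform. Estimate conception as next birth date minus gestational age from the medical birth register, using one stated convention for whether gestational age counts from conception or from the last menstrual period. This shows directly whether spacing shifted.
3. Beside the uncensored 18-month result, add a sensitivity analysis that ends follow-up at estimated next conception and expresses outcomes as rates, since follow-up time then differs between parents.

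The cost is small: the medical birth register is already among the linked sources, and gestational age already enters the outcome definitions. There are two drawbacks. Pregnancies that do not end in a registered birth are missed. Censoring also conditions on an event after the first birth that the reform may itself affect, so it can be informative and it changes the quantity estimated. The censored analysis should stay supportive only. Adding a 12-month window is not needed: it has the same defect to a lesser degree, with a threshold of 12 + 9 = 21 months.

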### Aim/objectives and research questions (RQ)

The aim of this project is to evaluate the consequences of parental leave policy in Sweden from a health equity perspective. More specifically, the project will cover the following RQ:

RQ#1: Is eligibility for earnings based parental leave benefits associated with parents’ mental health?

RQ#2: Is short birth spacing in relation to the speed premium supplement reform associated with health problems in the subsequent pregnancy of the mother (early pregnancy obesity) and the subsequent child (low birth weight, preterm and small-for-gestational age)?

RQ#3: Does the introduction and expansion of the father’s quota reserve days influence the mental health of parents after the birth of their child?

RQ#4: Does the introduction of simultaneous parental leave use through the double days reform influence parents’ mental health?

RQ#5: Does the introduction of the father’s quota and double days reforms influence children’s health (episodes of respiratory tract infections, childhood obesity) or health-related outcomes (duration of breast feeding)?

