### Study design and statistical analyses

A variety of advanced designs and statistical methods for observational data will be applied. First, using descriptive and correlational designs, we will implement standard multivariable methods to quantify links between prebirth health conditions, parental leave eligibility and uptake, and postbirth health outcomes while accounting for confounding using relevant covariates and heterogeneity analyses.

Second, we will use robust quasi-experimental approaches to assess the causal effects of parental leave policy on health, reducing the risk of selection effects and unmeasured confounding by harnessing the natural, ‘as-if’ randomisation around policies.^45 46^ With this approach, we can isolate the absolute policy effects on health even in the absence of detailed information on changes in parental leave uptake. These approaches include interrupted time series (ITS), regression discontinuity (RD) and difference-in-difference (DiD) designs. For ITS designs, segmented regression models will be adjusted for seasonality and trend while accounting for autocorrelation.^46^ For RD designs, continuity around the cut-off will be tested using the McCrary Density Test and similarity of eligible and ineligible observations will be determined through descriptive statistics. Finally, for DiD designs, we will examine the data to confirm parallel trends and other relevant assumptions.^45^

RQ#1: We will examine the effects of the 2002 doubling of flat-rate benefits on the mental health of parents. An RD design will be applied to plot psychiatric hospitalisation rates with labour income as a forcing variable, with separate plots before (with an income cut-off equivalent to 75 SEK, at 80% reimbursement rate) and after 2002 (with a cut-off equivalent to 150 SEK daily). Cut-offs for both parents’ income will be examined. We will triangulate our findings with a DiD approach, comparing those eligible for the increased benefits to those ineligible before and after reforms.

RQ#2: A segmented-regression ITS of monthly birth data comparing the rate of low birth weight and preterm births 3 years before and after the 1980 and 1986 speed premium reforms will be implemented. We will also compare the prevalence of obesity in mothers early in their second pregnancy before and after the reform.

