### Limitations

Despite our reliance on a robust quasi-experimental approach, it is difficult to predict the relative timing of the behavioural response to each parental leave reform (ie, in uptake) and its health consequences. Parents have been shown to respond quickly to policy changes,^14 15 27^ but given that some parents may not be aware of their eligibility on the reform dates, delayed reaction times could lead to lagged health effects for subgroups such as migrants.^12^ Thus, we will use a long follow-up both within the life course (ie, years since birth) and in the context of the policy (ie, years since reform implemented).

Quasi-experimental designs have the potential to reduce unmeasured confounding, but policies themselves, as well as ongoing trends, could inadvertently modify the composition of the study populations, potentially biasing any causal interpretations. For one, the speed premium may have affected the composition of individuals who decided to have children after the reform, that is, encouraging more parents eligible for earnings based benefits to have children after 1986, given their increased level of benefits for subsequent children. Exogenous impacts other than the policy under investigation could also contribute to changing population compositions, as in the case of the 1990s economic crisis, which may have discouraged couples with lower socioeconomic position from having children after the 1995 father’s quota. We will thus examine varying sociodemographic characteristics of the study populations before and after each reform to assess the robustness of the design to approximate causal effects, with corresponding subgroup and sensitivity analyses.

Registers generally have greater coverage than other data sources but may be prone to bias in the form of missing data and overcoverage (ie, unreported outmigration), which we will address in appropriate sensitivity analyses. The historical availability of register data may also influence our analytical choices. For example, to evaluate the impact of the father’s quota on psychiatric health, we will primarily look at the first reserved month introduced in 1995.^6^ However, only severe health outcomes (psychiatric hospitalisations) can be assessed with the available registers at that time. In order to evaluate less severe outcomes (outpatient visit and prescription data) of increased fathers’ leave use, we will evaluate the more recent double days reform.^16^

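### For RQ#2, a change in which women have a second birth may not be separable from an effect of spacing with the checks the article names; the mother's first-birth outcome in the same register would be a sharper control

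*Protocol article*

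**What the plan says.** In the protocol article, under Aim/objectives and research questions, RQ#2 asks: "Is short birth spacing in relation to the speed premium supplement reform associated with health problems in the subsequent pregnancy of the mother" and in the subsequent child. Study design and statistical analyses sets the method: "A segmented-regression ITS of monthly birth data comparing the rate of low birth weight and preterm births 3 years before and after" the two reforms. It adds a before-after comparison for the mother: "We will also compare the prevalence of obesity in mothers early in their second pregnancy before and after the reform". No comparison series is stated for either analysis.

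Limitations recognises a selection problem specific to this reform: "the speed premium may have affected the composition of individuals who decided to have children after the reform". The response is to compare sociodemographic characteristics before and after each reform, with matching subgroup and sensitivity analyses. Additional analyses lists subgroups by income or education, nativity, age and cohabitation. It also says of negative controls that "falsification outcomes (eg, prebirth hospitalisations) will also be considered".

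On sources, Data gives the start years: medical birth register (MBR) 1973, inpatient register 1964, total population register 1968, LISA 1990, social insurance database 1955, and censuses in 1985 and 1990. Covariates draws education, income and employment from LISA. Outcomes takes low birth weight, preterm birth and small-for-gestational age (SGA) from the MBR.

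**The concern.** A falsification outcome has to be something the exposure cannot affect. In RQ#3 to RQ#5 the exposure is leave taken after the birth, so admissions before the birth generally qualify. In RQ#2 the exposure is the interval that ends with the second birth. Admissions before that birth can fall in the very period the reform is meant to alter. The protocol itself expects stress and adverse reproductive outcomes in women who are pregnant while rearing a small child.

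Adverse birth outcomes are assumed here to recur within women. If the reform changes which women go on to a second child, second-birth rates can move with no effect of spacing. Because RQ#2 is worded as a question about spacing, that movement is bias. The stake is whether a break at 1980 or 1986 can be read as harm or benefit from shorter intervals.

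**Working it through.** The article gives no baseline rate, effect size or sample size for RQ#2, so there is no figure to reproduce. Three things can be checked.

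**1. Timing of the falsification window.** The caps are 24 months from 1980, "then with up to 30 months’ spacing (following a 1986 expansion"). Gestation of 9 months is the article's own assumption ("The WHO recommends a minimum of 24 months, assuming 9 months of gestation, before a new conception").

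- Latest conception within the 24-month cap: 24 − 9 = 15 months after the previous birth.
- Latest conception within the 30-month cap: 30 − 9 = 21 months.

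The spacing decision therefore precedes the second birth by about 9 months, and admissions during that pregnancy come after it. A count over the whole interval also changes mechanically if the interval shortens. Admissions before the first birth, or before the second conception, precede the exposure. The article does not say which window is meant.

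**2. Data for the two windows.** Three years either side of 1 January 1980 is 1977–1982; either side of 1 January 1986 is 1983–1988. LISA (1990 onwards) covers neither. The 1985 census falls in the second window only. The total population register and the social insurance database give partial cover. None of these describes obstetric history.

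MBR look-back to January 1973, for a second birth in:

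| Month of second birth | Look-back |
|---|---|
| January 1977 (start of 1980 window) | 4 × 12 = 48 months |
| January 1983 (end of 1980 window, start of 1986 window) | 10 × 12 = 120 months |
| January 1989 (end of 1986 window) | 16 × 12 = 192 months |

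First-birth records thus exist for both reforms. In the 1980 window the growing look-back would itself change the mix of intervals unless a maximum of 48 months or less is imposed. Both caps (24 and 30 months) lie inside that limit.

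**3. Size of a pure composition effect.** Every rate here is an assumption. Let p be the share of second-time mothers whose first birth was preterm, RR the recurrence risk ratio, and Δp the shift in p.

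Relative change in the second-birth preterm rate = Δp(RR − 1) / [1 + p(RR − 1)]

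With p = 5%, the denominator is 1.10 at RR 3 and 1.25 at RR 6:

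| Δp (percentage points) | RR 3 | RR 6 |
|---|---|---|
| 0.25 | 0.005/1.10 = 0.45% | 0.0125/1.25 = 1.0% |
| 0.5 | 0.010/1.10 = 0.9% | 0.025/1.25 = 2.0% |
| 1.0 | 0.020/1.10 = 1.8% | 0.050/1.25 = 4.0% |

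For comparison, a real effect from moving 5% to 10% of second births to short spacing at a risk ratio of 1.2 to 1.5 (also assumed) is share × (ratio − 1): 0.05 × 0.2 = 1.0% up to 0.10 × 0.5 = 5.0%.

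**Sensitivity of the proposed control.** Take a plain two-period comparison (two-sided 0.05, 80% power). A shift from 5% to 6% in the share with an adverse first birth needs about 8,158 births per period. The low birth weight shift it would cause needs 104,780 (low-risk rate 4%, RR 8) to 2,129,710 (low-risk rate 2%, RR 3). These counts ignore autocorrelation. They show only that the first-birth series reveals this selection far more readily than the outcome does.

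**The case against.** The strongest reply is that nothing here is an error. The falsification sentence offers one example and says only that such outcomes will be considered. The words that apply to all ITS designs open the sentence before it. Neither the window nor the birth is specified, and one legitimate reading (before the first birth) is feasible with inpatient data from 1964. All of that stands. A reader might infer that the article assigns RQ#2 an invalid test; the text does not support that.

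A reader might also infer that selection would simply pass as a reform effect. That goes too far as well. Limitations names this selection, and composition comparisons, subgroups and sensitivity analyses are planned. What remains is that these checks are sociodemographic and that their main source postdates both windows.

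Thirdly, a reader might conclude from the ranges above that the bias is as large as the effect sought. The documents supply none of the inputs. At a 0.25-point shift the bias is 0.45% to 1.0%, at or below the bottom of the assumed real effect. The larger shifts also need strong selection. If 10% of second births were newly induced, those women would need a preterm first-birth share of 10% for a 0.5-point shift (0.9 × 5% + 0.1 × 10% = 5.5%) or 15% for 1.0 point. The article predicts more parents eligible for earnings based benefits, not more with a preterm first birth.

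Finally, a condensed article need not list every negative control. That limits the point to a recommended improvement.

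**Conclusion.** The point holds in a limited form. For RQ#2, a reform-induced change in who has a second birth may not be separable from an effect of spacing using the checks the article describes. This rests on three features of the text: an ITS with no comparison series, composition checks that are sociodemographic and draw largely on a register starting in 1990, and one example of a falsification outcome that is clean only if its window stops early enough.

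The size and direction of any bias are unknown. Under the assumed rates, composition alone would move the second-birth preterm rate by about 0.5% to 4% relative for an upward shift in the share, and downward for the reverse. This shows that the issue is worth checking, not that it dominates. The change should be made, because a more direct check already sits in the planned data.

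**What to change.** For RQ#2:

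- **(a) Negative-control series.** Run the same segmented regression with the mother's first-birth low birth weight, preterm and SGA outcomes from the MBR as dependent variables, indexed by month of the second birth. Restrict this series and the matching second-birth series to one fixed maximum interbirth interval, 48 months or less for the 1980 reform. Report the estimated break with its confidence interval. Do not require that there be none: in total-population data a trivial break could fail such a rule.
- **(b) Adjusted model.** Report a sensitivity analysis of the second-birth outcomes adjusted for the first-birth outcome.
- **(c) Hospitalisations.** If they are used as a falsification outcome in RQ#2, end the window before the first birth or before the second conception. The former is simpler, because time at risk between the first birth and the second conception depends on spacing.

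The cost is one link within the MBR, one or two extra models, and the loss of longer intervals from this check. Since the reform could pull some births inside the interval limit, a break may partly reflect that and should be read accordingly. The control does not directly address the maternal obesity comparison.
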